#### **Study procedures**

The study team will visit the selected households and brief them about the survey objectives and process involved. After obtaining consent, information on basic demographic details, exposure history to laboratory-confirmed COVID-19 cases, symptoms suggestive of COVID-19 since March 2020, clinical history, COVID-19 testing and COVID-19 vaccination details will be recorded. All data will be entered in an Open Data Kit (ODK) application on mobile phones by the survey teams.

Trained phlebotomists in each survey team will collect 3 ml of venous blood from each participant. The serum will be separated after centrifugation in a local health facility and transported to the ICMR-NIE laboratory in Chennai.

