India started COVID-19 vaccination with BBV152 vaccine (Covaxin; Bharat Biotech) and ChAdOx1 nCoV-19 vaccine (COVID-19 Vaccine AstraZeneca) since January 16, 2021 under Emergency Use Authorization for the health care workers. The vaccination strategy was expanded for frontline workers in February 1, 2021 for frontline workers. In Phase 2 individuals above 60 years old and above 45 years old with specified comorbidities

became eligible for vaccination from March 1, 2021 followed by Phase 3 for all above 45 years of age from April 1, 2021. And finally Phase 4 for all above 18 years of age began on May 1, 2021 (6). Around 44 million individuals have received two doses while 160 million have received at least one dose of vaccine as on May 29, 2021 (7).

Population-based sero-epidemiological studies measure the presence of antibodies against SARS-CoV-2 (natural and vaccine induced) in different age groups. Repeated cross sectional serosurveys conducted in the same geographical location provide estimates to monitor trends over a period of and provide information valuable for the public health decision makers to design and revise containment strategies (8). The earlier serosurveys were conducted among individuals aged 10 years and above and seroprevalence among children below 10 years is still unknown. SARS-CoV-2 poses a high occupational risk to healthcare workers who are at the forefront of managing COVID-19 cases in hospital settings. The third serosurvey indicated seroprevalence around 25% among the HCWs. Also, the HCWs were prioritised for COVID-19 vaccination in the first phase of vaccine rollout in India owing to higher risk of exposure to infected persons.

In this context, it is proposed to conduct fourth round of serosurveillance to determine the prevalence of SARS-CoV-2 antibodies in the community and health care workers as per change in epidemiology and public health response to the epidemic in the country.

The objectives of the fourth survey are:

1. Estimate the prevalence of SARS-COV-2 antibodies among (a) children aged 6-17 y and (b) adults in the general population, at the national level
2. Estimate the prevalence of SARS-COV-2 antibodies among healthcare workers at the national level

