#### **Laboratory procedures**

All serum samples will be tested for presence of IgG antibodies against SARS-CoV-2 on the Advia Centaur Immunoassay system using the Siemens SARS-CoV-2 IgG Assay (Siemens Healthineers India, Mumbai) and Abbott Architect i2000SR automated

analyzer using the Abbott SARS-CoV-2 IgG assay (Abbott Park, IL, USA). The Siemens assay detects IgG antibodies against S1 protein of the receptor binding domain (S1-RBD) whereas the Abbott assay detects IgG antibodies against nucleocapsid (N) protein of SARS-CoV-2. The sensitivity and specificity of the Siemens IgG assay is 100% and 99.90% respectively (9), while the Abbott IgG assay has a sensitivity of 100% and specificity of 99.6% (9).

Testing procedures will be followed as per the manufacturer's instructions. Sera with indeterminate results will be repeat tested. For quality assurance, one percent of negative sera will be repeat tested. CLIA testing will be done at ICMR-NIE laboratory.

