### **Analysis plan**

#### **A] General population**

We will calculate the frequency of characteristics of survey participants. The reported occupations will be categorised into high and low risk considering the potential risk of exposure to known or unknown COVID-19 case.

We will estimate the seroprevalence of SARS-CoV-2 infection along with 95% confidence intervals using appropriate sampling weights and considering the cluster sampling used for the survey. We will define an antibody positive case as an individual whose sera tested positive on either of the two assays. Hence the sero-prevalence estimated will be based on presence of either N antibodies or S1-RBD antibodies. The final prevalence estimates will be calculated after adjusting for the IgG test performance characteristics of both assays.

We will use the survey data analysis module in STATA software (StataCorp LLC, Texas, USA).

We will separately estimate the seroprevalence of infections only among the adults. In order to maintain comparability with the previous surveys, we will randomly select one adult survey participant per household from the survey database.

We will estimate proportion of individuals with COVID-19 vaccination along with 95% CI. We will also estimate the seroprevalence with 95% CI for SARS-CoV-2 infection by age, sex, locality, occupation, symptom status, contact history, RT-PCR testing and confirmation status.

We will estimate the infection-to-case ratio as the number of individuals with SARS-CoV-2 infection (as per IgG detection) compared to the number of RT-PCR reported cases of COVID-19. We will apply the seroprevalence to the total population above 10 years projected for the year 2020 using 2011 census data to estimate the number of infections in the country. The published literature indicates that the IgG antibodies against SARS-CoV-2 infection start appearing by the end of first week, and most cases are IgG positive by the end of the second week (10). We will consider the number of reported COVID-19 cases 15 days and one week before the initiation of serosurvey to estimate the plausible range of the number of infections. We will estimate the range of the infection fatality ratio (IFR) assuming a three-week lag time from infection to death (11,12)

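### Seroprevalence by symptom status mixes infection with vaccination: a dose can make an adult antibody positive and, through a reported reaction, symptomatic, and the table is not split by vaccination status

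*Combined protocol and SAP*

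**What the plan says.** Four parts of the combined protocol and SAP bear on this point.

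- **Study procedures.** At interview, "symptoms suggestive of COVID-19 since March 2020, clinical history, COVID-19 testing and COVID-19 vaccination details will be recorded". The text gives no symptom list, does not relate onset to a dose, and sets aside no period after a dose.
- **Background.** Roll-out started on January 16, 2021 with health care workers. "And finally Phase 4 for all above 18 years of age began on May 1, 2021". By May 29, "Around 44 million individuals have received two doses while 160 million have received at least one dose of vaccine". The survey is dated June to July 2021. The background also says that surveys of this kind "measure the presence of antibodies against SARS-CoV-2 (natural and vaccine induced) in different age groups".
- **Laboratory procedures and Analysis plan, A] General population.** The Siemens assay targets S1-RBD and the Abbott assay targets N. "We will define an antibody positive case as an individual whose sera tested positive on either of the two assays", so S1-RBD alone is enough.
- **Analysis plan, A] General population.** "We will also estimate the seroprevalence with 95% CI for SARS-CoV-2 infection by age, sex, locality, occupation, symptom status, contact history", followed by RT-PCR testing and confirmation status. Vaccination status is not in that list. The only stated use of the vaccination data is to estimate the share vaccinated, with its confidence interval.

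**The concern.** The symptom variable and the antibody result share a cause that is not infection. Vaccination can produce S1-RBD antibody, which the background accepts. If a participant reports fever or aches after a dose as COVID-like symptoms, the same dose also places that person in the symptomatic row. A table labelled as infection by symptom status then partly shows who was vaccinated.

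This is new in the fourth round. The third survey ended on January 6, 2021, ten days before roll-out, so the same symptom question raised no such problem then. It concerns adults: under the phases listed in the background, children were not yet eligible.

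At stake is the reading of one planned breakdown: how much more often people with symptoms were infected than people without.

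**Working it through.** **No plan figure applies.** The plan's one calculated number is the sample size for ages 6-9, 2 × 1.96² × 0.30 × 0.70 / 0.03² = 1792.7. It agrees with the stated 1792 and has no bearing here. What follows is an illustration of the mechanism.

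**Inputs, all assumed.** The documents give the count vaccinated but no population denominator, and no reaction rate, seroconversion rate or symptomatic fraction.

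- p = 0.50 infected, all of them seropositive
- s = 0.10 or 0.30, symptomatic among the infected
- b = 0.05, background symptoms in the uninfected
- v = 0.20 to 0.35, vaccinated adults, independent of infection
- c = 0.80, seroconversion in uninfected vaccinees
- r = 0.10 to 0.40, vaccinees who report a reaction as a symptom
- Assay error is ignored.

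**Formulas.** In vaccinees, s' = 1 − (1−s)(1−r) and b' = 1 − (1−b)(1−r).

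- Infected and symptomatic: X = p[(1−v)s + v s']
- All symptomatic: S = X + (1−p)[(1−v)b + v b']
- Seroprevalence, symptomatic: [X + (1−p) v c b'] / S
- Seroprevalence, asymptomatic: [p − X + (1−p) v c (1−b')] / (1−S)

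**Worked case: s = 0.10, v = 0.20, r = 0.10.**

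- s' = 0.19 and b' = 0.145.
- X = 0.5(0.08 + 0.038) = 0.059.
- S = 0.059 + 0.5(0.04 + 0.029) = 0.0935.
- Symptomatic: (0.059 + 0.0116)/0.0935 = 75.5%.
- Asymptomatic: (0.441 + 0.0684)/0.9065 = 56.2%.
- Gap: 19.3 points.

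With no vaccination the gap is 0.05/0.075 − 0.45/0.925 = 66.7% − 48.6% = 18.0 points. This is the infection contrast that the table's label promises.

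| s | v | r | Symptomatic | Asymptomatic | Gap (points) | Ratio |
|---|---|---|---|---|---|---|
| 0.10 | 0 | – | 66.7% | 48.6% | 18.0 | 1.37 |
| 0.10 | 0.20 | 0.10 | 75.5% | 56.2% | 19.3 | 1.34 |
| 0.10 | 0.35 | 0.10 | 80.1% | 62.1% | 18.1 | 1.29 |
| 0.10 | 0.35 | 0.40 | 84.7% | 58.7% | 26.0 | 1.44 |
| 0.30 | 0 | – | 85.7% | 42.4% | 43.3 | 2.02 |
| 0.30 | 0.35 | 0.30 | 89.3% | 55.0% | 34.3 | 1.62 |

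Gaps and ratios come from unrounded values. Two effects oppose each other. Reactions counted as symptoms widen the gap. Vaccine-induced positives among people without symptoms raise the asymptomatic row and narrow it.

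**Null case.** Let symptoms be unrelated to infection (5% in both groups), with v = 0.20. With r = 0 the table reads 58.0% against 58.0%. With r = 0.30 it reads 75.0% against 56.0%, a false gap of 19.1 points. With v = 0.10 and r = 0.10 it reads 59.7% against 53.6%, about 6 points. A second set of assumptions (30% infected, 10% symptomatic in both groups, coverage 10-30%, seroconversion 60-90%, reactions 10-50%) gives false gaps of 3.5 to 33.1 points.

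**Does excluding post-dose symptoms suffice?** Perfect exclusion sets r = 0 and leaves vaccine-induced positives in the table.

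- s = 0.10, v = 0.20: (0.05 + 0.004)/0.075 = 72.0% against (0.45 + 0.076)/0.925 = 56.9%, a gap of 15.1. The truth is 18.0, and the untreated reading at r = 0.10 was 19.3.
- s = 0.10, v = 0.35: the gap is 13.0, against 18.1 untreated at r = 0.10.

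In both cases exclusion moves the contrast further from the truth. Restricting to the unvaccinated sets v = 0 and returns 18.0.

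**The case against.** The strongest reply is that this is mainly a by-product of counting vaccine-induced antibody as infection with no vaccination stratum. Splitting the table by vaccination status deals with both, and a symptom-timing rule alone may do harm. That stands, and it determines the remedy. What remains specific to symptoms is shown by the null case: with no reactions reported as symptoms there is no false gap, and with them there is one.

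Four stronger readings are tempting, and the documents do not support them.

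- *The contrast must be biased toward symptomatic.* The table above shows the gap wider, unchanged or narrower, depending on inputs that the documents do not give.
- *The symptomatic share of seropositives, or its comparison across ages, is biased.* The plan lists seroprevalence within symptom groups. It plans neither of these quantities; age and symptom status are separate entries in one list.
- *The problem cannot be repaired after fieldwork.* Vaccination details are recorded, so an unvaccinated table needs no new data. Only separating reactions from illness within vaccinees needs timing relative to a dose.
- *The questionnaire ignores timing.* The ODK form is not among the documents. It may ask for onset and dose dates; the protocol does not say.

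It is also fair to object that the resemblance between vaccine reactions and the symptoms asked about is an outside premise. It is plausible, but it remains an assumption.

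**Conclusion.** The concern holds as a minor one. As written, the symptom-status table for vaccine-eligible adults does not isolate infection, because vaccination can act on both the row a person falls in and the antibody result. The illustrations run from almost no change in the gap (18.0 to 18.1 points) to a widening of 8 points (18.0 to 26.0) and a narrowing of 9 (43.3 to 34.3). Where there is no true association, the false gaps run from 3.5 to 33.1 points. All of these rest on assumed coverage, reaction rate, seroconversion and symptomatic fraction, so they show that the effect can matter and not how large it will be.

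A reader might infer that the survey's main estimates are at risk. They are not, on this ground: the objectives are antibody prevalence in children, adults and health care workers, and none depends on symptom status.

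**What to change.** In the Analysis plan for the general population, state that seroprevalence by symptom status will be shown separately for vaccinated and unvaccinated participants, and that any statement about infection by symptom status will rest on the unvaccinated stratum.

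Optionally, if the ODK form does not already do so, record whether symptoms began only within a few days after a dose. Use this as a sensitivity definition within the vaccinated stratum, not as the sole remedy. It costs one or two questions, depends on recall, and will reclassify some true infections with onset soon after a dose.

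The main change needs no new data. Its cost is precision: at an assumed 20-35% coverage, the 19,600 planned adults leave 15,680 to 12,740 unvaccinated. Confidence intervals widen by a factor of about 1/√0.80 = 1.12 to 1/√0.65 = 1.24 if the design effect is unchanged. The groups vaccinated first, mainly older adults, will be under-represented, so the result should be described as applying to unvaccinated participants.

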#### **Study duration**

Two months including data collection and analysis.

#### **Laboratory procedures**

All serum samples will be tested for presence of IgG antibodies against SARS-CoV-2 on the Advia Centaur Immunoassay system using the Siemens SARS-CoV-2 IgG Assay (Siemens Healthineers India, Mumbai) and Abbott Architect i2000SR automated

analyzer using the Abbott SARS-CoV-2 IgG assay (Abbott Park, IL, USA). The Siemens assay detects IgG antibodies against S1 protein of the receptor binding domain (S1-RBD) whereas the Abbott assay detects IgG antibodies against nucleocapsid (N) protein of SARS-CoV-2. The sensitivity and specificity of the Siemens IgG assay is 100% and 99.90% respectively (9), while the Abbott IgG assay has a sensitivity of 100% and specificity of 99.6% (9).

Testing procedures will be followed as per the manufacturer's instructions. Sera with indeterminate results will be repeat tested. For quality assurance, one percent of negative sera will be repeat tested. CLIA testing will be done at ICMR-NIE laboratory.

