### **Sample size**

#### A] General population

We plan to enrol 28,000 individuals (19,600 individuals in the age group  $\geq 18$  years, 5600 children in the age group of 10-17 years and 2,800 children in the age group of 6-9 years) across the country by allocating a minimum of 400 individuals to each of the 70 districts that were included in the earlier survey. We have divided the overall sample size of 28,000 in the above-mentioned age groups as per age structure of the population (Census 2011).

The sample size assuming a seroprevalence of 30%, with 10% relative precision, for 95% CI and design effect of 2 would be 1792 for children in the 6-9 age group. The required sample size is sufficient to estimate prevalence for each age group. However, in order to have a sufficiently large sample for a national level survey, we will keep the same overall sample size for the fourth serosurvey.

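### The assay adjustment takes 100% sensitivity for both assays with no interval, so it can only lower prevalence, and the plan does not say how assay uncertainty enters the confidence interval

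*Combined protocol and SAP*

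**What the plan says.** Laboratory procedures gives each assay one sensitivity and one specificity: "The sensitivity and specificity of the Siemens IgG assay is 100% and 99.90% respectively". For the Abbott assay the values are 100% and 99.6%. No interval, panel size or time since infection accompanies them. The two assays target different antigens, S1-RBD (Siemens) and nucleocapsid (Abbott).

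The Analysis plan for the general population sets a parallel rule: "We will define an antibody positive case as an individual whose sera tested positive on either of the two assays". It then says: "The final prevalence estimates will be calculated after adjusting for the IgG test performance characteristics of both assays". It does not give the formula, the combined Se and Sp of the rule, or any sensitivity analysis over them. The only components named for the 95% CI are in the phrase "using appropriate sampling weights and considering the cluster sampling used for the survey". The same section applies the seroprevalence to the projected population to obtain a number of infections, an infection-to-case ratio and an infection fatality ratio (IFR).

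On available data, Study procedures says that "symptoms suggestive of COVID-19 since March 2020, clinical history, COVID-19 testing and COVID-19 vaccination details will be recorded". Sampling method keeps people with past laboratory-confirmed infection in the survey (current cases in home isolation are left out). The Analysis plan already lists seroprevalence by RT-PCR testing and confirmation status.

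**The concern.** An adjustment with Se = 100% removes expected false positives and does nothing else. It assumes that no one with past infection tests negative on both assays. The Analysis plan itself is more cautious: it notes that most cases, not all, have detectable IgG two weeks into infection.

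The stated values are also estimates from validation panels of unstated size. An observed 100% still has a lower confidence limit, and the plan does not say whether that uncertainty will reach the reported CI. Prevalence read as infection, the infection-to-case ratio and the IFR are the outputs exposed. Missed infections would push the first two down and the IFR up.

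**Working it through.** **Inputs.** Se 1.00 and 1.00, Sp 0.999 and 0.996 (Laboratory procedures). Planning prevalence 30%, design effect 2, n = 28,000 overall and 2,800 for ages 6-9 (Sample size). Third survey 24.1%, CI 23.0 to 25.3 (introduction). Combined Se below 100%, raw prevalence other than 30%, and panel sizes are assumptions.

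**1. The plan's own figure.** "The sample size assuming a seroprevalence of 30%, with 10% relative precision, for 95% CI and design effect of 2 would be 1792". Check: 2 × 1.96² × 0.30 × 0.70 / 0.03² = 2 × 896.4 = 1792.7. It reproduces and is not affected by this point.

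**2. Combined inputs under the either-positive rule.**
- Se = 1 − (1 − 1)(1 − 1) = 1.
- Sp = 0.999 × 0.996 = 0.9950 if false positives are independent. The bounds are 1 − (0.001 + 0.004) = 0.995 if they never coincide and 0.996 if they overlap fully.

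**3. Direction.** Rogan-Gladen: adjusted = (raw + Sp − 1)/(Se + Sp − 1). With Se = 1, adjusted − raw = −(1 − raw)(1 − Sp)/Sp, which is never positive.
- Raw 30%: −0.70 × 0.005/0.995 = −0.35 points, giving 29.65%.
- Raw 50%: −0.25 points.
- The largest possible subtraction is 0.005/0.995, about 0.50 points.

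**4. If combined Se is lower** (assumed values; raw 30%, Sp 0.995). The infection count scales by 0.995/(Se − 0.005). The infection-to-case ratio scales by the same factor and the IFR by its inverse, wherever an infection sensitivity properly applies.

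| Combined Se | Adjusted prevalence | Shift from Se = 100% | Infections × | IFR × |
|---|---|---|---|---|
| 100% | 29.65% | 0 | 1.00 | 1.00 |
| 98% | 30.26% | +0.61 | 1.02 | 0.98 |
| 95% | 31.22% | +1.57 | 1.05 | 0.95 |
| 90% | 32.96% | +3.31 | 1.11 | 0.90 |

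**5. Against sampling error.** Half-width = 1.96 × √(deff × p(1 − p)/n).
- National, deff 2, p = 30%: 1.96 × √(2 × 0.21/28,000) = 0.76 points. The shift exceeds this only if combined Se is below about 97.5%.
- Third survey: (25.3 − 23.0)/2 = 1.15 points. If its n was also 28,000 (assumed), the simple-random half-width at 24.1% is 0.50, so the implied deff is (1.15/0.501)² ≈ 5.3. At p = 30% the threshold is then about 96%.
- Ages 6-9, n = 2,800, deff 2: half-width 2.40 points, threshold about 92.5%.
- At a raw 50% (assumed), deff 2, the national threshold rises to about 98.4%.

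**6. What an observed 100% leaves open.** With all m positives detected, the exact 95% lower limit is 0.025^(1/m). Taking that limit as the combined Se, at a raw 30%:

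| Assumed m | Lower limit | Shift (points) |
|---|---|---|
| 50 | 92.9% | up to 2.28 |
| 100 | 96.4% | up to 1.12 |
| 200 | 98.2% | up to 0.55 |
| 500 | 99.3% | up to 0.22 |

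**The case against.** The strongest reply is that the either-positive rule itself protects sensitivity. If misses are independent, two assays at 90% combine to 99% and two at 80% to 96%. A combined 95% would need each assay near 78% (1 − √0.05 = 0.776). That stands, although correlated misses would give less. It is why the size of the problem cannot be fixed from the documents.

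A reader might infer that the reported CI will leave out assay error and that this is its largest error source. The documents do not support either statement. The plan is silent on the variance method, and silence is not a decision to omit. Whether assay error outweighs sampling error depends on an unknown combined Se. At 98% and a raw 30% the shift of 0.61 points is below both half-widths.

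A reader might also infer that 100% sensitivity contradicts the either-positive rule, since a second perfect assay adds only false positives. That holds only if the target is past infection. The objectives are antibody prevalence, and the introduction counts natural and vaccine-induced antibodies. Each assay can be fully sensitive for its own antibody while the two together identify more people.

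Finally, dividing the whole seropositive fraction by an infection sensitivity would inflate infections, because the fraction includes vaccine-induced S1-RBD positives. The introduction reports 160 million people with at least one dose. This objection is right and limits the remedy to unvaccinated participants.

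**Conclusion.** The point holds in limited form. Applied as stated, the inputs give a one-way correction of at most about 0.5 points that cannot correct for missed infections. The plan does not state the combined Se and Sp, the formula, or the treatment of their uncertainty.

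The consequence is conditional. At a raw 30%, an assumed combined Se of 98, 95 or 90% moves the estimate by 0.6, 1.6 or 3.3 points. That exceeds national sampling error only below roughly 96 to 97.5%, and for ages 6-9 only below about 92.5%. These figures assume the Rogan-Gladen form, Sp of 99.5%, and design effects of 2 to about 5.3.

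The antibody estimate named in the objectives can stand as planned, provided its interval is specified. The infection estimate, infection-to-case ratio and IFR need a companion analysis. No change to sampling or sample size is needed.

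**What to change.** 1. Keep the planned antibody estimate with Se = 100%. State the formula and the either-rule inputs: Sp about 99.5% if errors are independent, 99.5 to 99.6% over any overlap.
2. Say how Se and Sp uncertainty enters the 95% CI. One option is a cluster bootstrap with beta draws for each assay's Se and Sp, based on the validation panel sizes, which should be stated.
3. Beside it, for unvaccinated participants only, report infection prevalence adjusted for field sensitivity. This group includes ages 6-17, since the introduction describes eligibility only for adults. Estimate the either-rule sensitivity among unvaccinated participants with a laboratory-confirmed infection more than 14 days before blood draw. If that subgroup is small, use a stated range of Se instead.
4. Show the effect on the infection-to-case ratio and IFR as a sensitivity analysis, naming the population it is applied to. Do not apply this infection sensitivity to vaccinated participants.

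**Cost.** Extra analysis, no new samples. The date of the positive test is needed, and the plan does not say that it is recorded. Intervals will widen. The field sensitivity may be biased up, because confirmed cases may be more severe than average, or down, through misreported or false-positive tests. It should therefore stand beside the planned result and not replace it.
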